#### Blinding

This is an open-label trial as the intervention cannot be blinded. Given the nature of the primary endpoint, the risk for ascertainment bias is considered negligible. Follow-up data collection is centralized and will be done by blinded personnel.

#### Schedule

The schedule and timelines are presented in Tables 1 and 2.

**Table 1 Tab1:** Timeline related to the clusters wit hin one participating unit

Timeline Cluster (Surgeon)									
Time points are related to start of StOP? implementation per cluster	before intervention	up to -4 week to start of intervention	up to 2 weeks to intervention	first 2 weeks of intervention	during intervention, for each operation	1 mo after start of intervention	2 mo after start of intervention	3 mo after start of intervention	4 mo after start of intervention
**All surgeons **									
Surgeon recruitment	X								
Eligibility screening	X								
Informed consent	X								
Allocation to intervention or control group		X							
Demographic data collection		X							
Hospital and surgical unit characteristics	X	X							
Measuring adherence with StOP? Protocol / if StOP?s were performed (questionnaires filled out by the scrub nurses)					X				
**Surgeons in the intervention group**									
StOP? training and on-site feedback			X	X					
Feedback and refresher training						X	X	X	
End of intervention report									X

**Table 2 Tab2:** Timeline related to the collection of operation and patient-related data

Timeline of aquisition of patient and operation related data	During intervention, for each operation	End of every week of intervention	1 month after start of intervention	2 month after start of intervention	3 month after start of intervention	4 month after start of intervention	5+ month after start of intervention
**Measuring adherence**							
Measuring adherence with StOP? Protocol (questionnaires filled out by the scrub nurses)	X						
Basic characteristics of operations		X					
Generation of patient key		X					
**Measuring patient characteristics and outcomes**							
Patient and operation characteristics and outcome data			X	X	X	X	X

#### Study schedule

Figure 2 shows the timeline related to the participating units. Note that units are grouped according to their geographic location, because the intervention requires a high level of presence of the researchers in participating units. The study is performed in 40 centers that include university and tertiary centers in Switzerland, Germany, and Austria. Recruitment of centers is ongoing. Currently, letters of commitment are available from 28 centers.

**Fig. 2 Fig2:**
[figure not shown]
Timeline for the participating surgical units

### Regulatory aspects and safety

#### Local regulations/Declaration of Helsinki

This study is conducted in compliance with the protocol, the current version of the Declaration of Helsinki, ICH-GCP in analogy, and applicable national regulations, i.e., the Human Research Act in Switzerland as well as other locally relevant legal and regulatory requirements.

#### (Serious) adverse events and notification of safety and protective measures

StOP? II is regulated by chapter 4 of the Clinical Trial Ordinance. Chapter 4 describes the safety documentation and notification requirements for serious adverse events (SAEs). It defines (Art. 63) SAEs that have to be documented (and reported) as any event which:Requires inpatient treatment not envisaged in the protocol or extends a current hospital stayResults in permanent or significant incapacity or disabilityIs life-threatening or results in deathCauses a congenital anomaly or birth defect

And it cannot be excluded that the event is attributable to the intervention.

Given the nature of the intervention, we submit that Article 63 is not directly applicable to this trial. Unless there are specific reasons to assume an involvement of the StOP?-protocol, we will not routinely record serious adverse events and therefore also not foresee this in the case report forms and standard operating procedures. We base this decision on the following reasons: (1) the intervention is not directly applied to patients; (2) the nature of the intervention and the perceived mechanism practically exclude any direct effects; rather, the intervention entails its effects (if any) indirectly (see Methods/design); consequently, we can a priori exclude any relationship between the intervention and the events listed above; (3) even establishing a temporal relationship of any untoward medical occurrences to the intervention is difficult to operationalize; (4) finally, we fear that the heterogeneity of the underlying operations and the patient population would result in a high number of recorded events (if any event is documented) and actually blur any safety issues.

Instead, we record relevant data with regard to safety as primary and secondary endpoints. 

#### Reporting of serious adverse events

Not applicable as described above

#### Follow-up of serious adverse events

Not applicable as described above

#### Notification of safety and protective measures

If immediate safety and protective measures have to be taken during the conduct of the study, the investigator notifies the responsible ethics committee of these measures, and of the circumstances necessitating them, within 7 days.

#### (Periodic) safety reporting

An annual safety report (ASR/DSUR) containing relevant safety information from all sites is provided by the sponsor. Relevant safety information in this case means descriptive statistics of accumulating primary and secondary endpoint events pooled across trial arms. Pooling of trial arms is necessary to avoid multiple testing. The sponsor distributes the ASR/DSUR to all the participating Investigators. It is submitted once a year to the local ethics committee by the investigator.

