#### Interim analyses

We will conduct one interim analysis after endpoint data were completely collected for 200 clusters. We will reassess the ICC based on the data collected to adjust the sample size if needed. To calculate the ICC, we will use multilevel mixed-effects logistic regression. If the ICC is > 0.024, we will perform new power calculations using the same assumptions as in the original sample size calculation. Based on these calculations, we will increase the number of clusters and/or the number of patients per cluster except if the required increase would be too large to be feasible. Because the type I error is not affected by the recalculation of the ICC, we will not adjust the significance level.

Moreover, an interim analysis of the primary outcome will be performed to examine the trial for potential futility: The conditional power for a statistically significant difference between the intervention and control groups at the end of the study will be estimated based on data collected at the time of the interim analysis. If the conditional power is < 20%, it is recommended to terminate the trial for futility. Implications for type I and II errors are minimal, so no adjustment is needed for this type of interim analysis [45].

Given that no interim analysis for safety or efficacy will be done, no independent Data Monitoring Board (iDMC) is established, and possible sample size adaptations or trial termination for futility will be decided by the Steering Committee.

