#### (Premature) termination of study

The sponsor may terminate the study prematurely according to certain circumstances, e.g.:○ Ethical concerns○ Insufficient participant recruitment○ Alterations in accepted clinical practice that make the continuation of the study unwise○ Early evidence of harm of the experimental intervention

Upon regular study termination, the Ethics Committee is notified within 90 days.

Upon premature study termination or study interruption, the Ethics Committee is notified within 15 days.

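### The annual safety report is pooled on a mistaken multiple-testing ground, and no by-arm harm criterion supports the protocol's termination ground of early evidence of harm

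*Protocol article*

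**What the plan says.** Four sections of the protocol article bear on this.

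- **(Serious) adverse events and notification of safety and protective measures:** "Unless there are specific reasons to assume an involvement of the StOP?-protocol, we will not routinely record serious adverse events". The endpoints take their place: "Instead, we record relevant data with regard to safety as primary and secondary endpoints".
- **(Periodic) safety reporting:** "Relevant safety information in this case means descriptive statistics of accumulating primary and secondary endpoint events pooled across trial arms". The reason given is "Pooling of trial arms is necessary to avoid multiple testing". The report is circulated widely: "The sponsor distributes the ASR/DSUR to all the participating Investigators". It also goes to the ethics committee each year.
- **Interim analyses:** "We will conduct one interim analysis after endpoint data were completely collected for 200 clusters". Besides re-estimating the ICC, this look assesses mortality for futility. It estimates from the accumulated data the conditional power for a significant difference between the groups, and recommends stopping below 20%. No alpha adjustment is made, and the Steering Committee decides. The section then states: "Given that no interim analysis for safety or efficacy will be done, no independent Data Monitoring Board (iDMC) is established".
- **(Premature) termination of study:** one example of a ground on which the sponsor may stop is "Early evidence of harm of the experimental intervention".

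**The concern.** Harm from the intervention is a contrast between arms. The endpoints are the safety data, yet the only recurring report of them removes that contrast, and the reason given for removing it is a statistical error. The termination ground therefore has no planned recurring review and no criterion behind it.

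The one by-arm look is made for another purpose. Its conditional power refers to a significant difference without saying in whose favour, and the final test is two-sided. Read literally, a strong trend towards harm counts as a high chance of success.

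At stake is whether an excess of deaths in one arm of an open-label trial with mortality as its primary endpoint would be recognised in time, and under which rule.

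**Working it through.** **1. The plan's own power figure.** Inputs from Sample size calculation: 200 clusters per arm, mean size 24, coefficient of variation 0.5, ICC 0.024, mortality 1.8% against 0.9%, two-sided 0.05.

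- Design effect = 1 + 0.024 × (24 × 1.25 − 1) = 1.696.
- Effective number per arm = 4,800 / 1.696 = 2,830.
- Power = 83.5%, against 84% stated. The plan's figure is reproduced, so the same adjustment is used below.

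**2. What the pooled report can show.** With control mortality p = 1.8%, an odds ratio OR gives intervention mortality q = o/(1 + o), where o = OR × 0.018/0.982. The pooled rate is (p + q)/2.

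| OR | Intervention | Pooled |
|---|---|---|
| 0.5 | 0.91% | 1.35% |
| 1 | 1.80% | 1.80% |
| 1.5 | 2.68% | 2.24% |
| 2 | 3.54% | 2.67% |

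The pooled rate rises under harm, but 2.67% is also what a case mix with 2.67% mortality in both arms and no effect would give. The pooled figure cannot separate the two.

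**3. What by-arm data can show at 200 clusters.** Assume 100 clusters of 24 per arm, that is 2,400 operations per arm. The harm odds ratios are assumptions. z = (p − q)/√[(p(1 − p) + q(1 − q)) × 1.696/2,400], negative towards harm.

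- OR 2: 2,400 × 0.018 = 43 deaths against 2,400 × 0.03536 = 85. z = −0.01736/0.00605 = −2.87 (−3.7 without clustering). The chance that z falls below −1.96 is about 82%.
- OR 1.5: 43 against 64 deaths, z = −1.58. The same chance is about 35%.

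**4. Does looking by arm cost type I error?** Stopping for harm only removes trials that might otherwise have gone on to claim benefit, so the false-benefit rate cannot rise. A simulation of 1,000,000 trials, with two assumed harm-only looks at 1/3 and 2/3 of the information and boundaries of z from 1.645 to 3.0, agrees:

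- False claims of benefit: 0.0248 to 0.0253, against 0.0250 without looks (simulation error about 0.0002).
- Power: 84.0% to 84.1% when set at 84%.
- By contrast, three unadjusted two-sided looks at 0.05, each allowed to reject, give 10.8%.

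Multiplicity arises only when looks are used to claim an effect. The Interim analyses section itself makes an unadjusted comparison of mortality between arms, which does not fit the reason given for pooling.

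**5. Does the futility rule catch harm?** Take an interim z at half the information (t = 0.5) and project the current trend, since the plan estimates conditional power from the interim data. The projected final z has mean z/√0.5 and standard deviation √0.5.

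- *No direction, as written, OR 2:* mean −2.87/0.707 = −4.06. The chance that the final z is below −1.96 is Φ((4.06 − 1.96)/0.707) = 99.8%, far above 20%, so the rule says continue.
- *No direction, OR 1.5:* mean −2.23, conditional power about 65%; continue.
- *Read as power to show benefit:* under OR 1.5 the chance of falling below 20% is 99% on the current trend, or 92% if the design effect is assumed for the remaining data. The trial would probably stop, but labelled futile.
- *No direction, but design effect assumed for the remainder, OR 2:* about 2%; stop.

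The outcome depends on a reading that the text does not fix.

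**The case against.** **By-arm evidence does exist.** A reader might infer that the harm ground can never be met from trial data. The protocol does not support that. The 200-cluster analysis compares mortality by arm, and a doubling of the odds would be visible there. An ad hoc route also remains for events with specific reasons to suspect the intervention, although the same section holds that a relationship can be excluded a priori. The termination list is a set of examples and does not require the evidence to come from the annual report, so there is no strict contradiction. This objection stands. What remains is that the look occurs once, halfway, under a futility label and without a harm criterion.

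**A doubling would not go unnoticed.** A reader might infer that the pooled report would look normal under serious harm. At the planned baseline it would not: 2.67% against 1.80% is about 48% higher. It looks reassuring only if a lower control rate is set against the 1.8% benchmark. The supportable statement is that a rise cannot be attributed to an arm.

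**Pooling and light monitoring are defensible.** The intervention is a 30–90 second briefing that the protocol likens in risk to a time-out, and earlier data pointed to lower mortality. Withholding by-arm results from all investigators protects an open-label trial. This is a good reason for pooling the circulated report, but it is not the reason given, and it does not prevent a confidential by-arm review.

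**Conclusion.** The point holds in limited form. The multiple-testing reason for pooling is wrong whatever values are assumed. No recurring by-arm review and no harm criterion supports the termination ground, and the one by-arm look has no stated direction. Read literally on the current trend, that look gives a conditional power of about 99.8% when the odds of death have doubled, and so recommends continuing.

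The figures rest on the planned 1.8% control mortality, 24 operations per cluster, an equal split of the 200 clusters and the plan's use of the ICC. The harm odds ratios are illustrative. Without clustering, z for a doubling moves from about 2.9 to 3.7. The protocol does not show that harm could never be detected, nor that the circulated report should be unpooled.

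**What to change.** 1. Delete the sentence on multiple testing. Keep the circulated annual report pooled and give trial integrity as the reason.
2. Add a pre-specified, one-sided, harm-only criterion for deaths to the existing 200-cluster look. State that the futility conditional power refers to benefit.
3. At each annual report, have CTU staff independent of the investigators prepare a closed by-arm table of the endpoint events, released only if the criterion is crossed. The protocol says that an independent CTU data manager performs the allocation, but not which statistician may see it, so name the role and an independent recipient.
4. State that none of this can support a claim of benefit, so the 0.05 level is unchanged, and reconcile the sections on interim analyses, periodic safety reporting and premature termination.

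The cost is protocol and SAP wording, one closed table from data already collected, and a false-alert risk set by the boundary. With no true effect, a single look alerts in 2.5%, 1% or 0.1% of trials at z of 1.96, 2.326 or 3.0. The two simulated looks gave 4.1%, 1.7% and 0.25%. A stricter boundary also detects less: at 200 clusters a doubling would cross these in about 82%, 71% and 45% of trials. The choice of boundary belongs to the sponsor. No extra patients or visits are needed.

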#### Amendments

Substantial changes to the study setup and study organization, the protocol, and relevant study documents are submitted to the Ethics Committee for approval before implementation. Under emergency circumstances, deviations from the protocol to protect the rights, safety, and well-being of human subjects may proceed without prior approval of the Ethics Committee. Such deviations shall be documented and reported to the Ethics Committee as soon as possible.

Substantial amendments are changes that affect the safety, health, rights, and obligations of participants, changes in the protocol that affect the study objective(s) or central research topic, changes of study site(s), or of study leader and sponsor.

A list of substantial changes is also available on www.swissethics.ch.

A list of all non-substantial amendments will be submitted once a year to the responsible Ethics Committee together with the ASR.

#### (Premature) termination of study

The sponsor may terminate the study prematurely according to certain circumstances, e.g.:○ Ethical concerns○ Insufficient participant recruitment○ Alterations in accepted clinical practice that make the continuation of the study unwise○ Early evidence of harm of the experimental intervention

Upon regular study termination, the Ethics Committee is notified within 90 days.

Upon premature study termination or study interruption, the Ethics Committee is notified within 15 days.

#### Insurance

To compensate trial participants for study-related damage or injuries, liability is provided per local regulations.

#### Confidentiality and coding

Trial and participant data will be handled with utmost discretion and is only accessible to authorized personnel who require the data to fulfill their duties within the scope of the study. On the CRFs and other study-specific documents, participants are only identified by a unique participant number.

The following data will be centrally stored:Characteristics of participating hospitals (hospital data)Characteristics of participating clinical departments (department data)Characteristics of participating surgeons including allocated trial arm and training details (surgeon data)Patient keyCharacteristics, operation, and outcome data of the patient (patient data)Adherence to the StOP?-protocol

Linkage of data will be ensured via unique keys. Data 1–4 will be stored in a GCP-compliant trial management system on the same server. Data 1, 2, and 4 do not contain directly identifying person data. The surgeon data (#3) contains the name of the surgeon. This will be mentioned explicitly in the informed consent. The identifying data of the surgeon will only be visible for data entry personnel. The system prohibits to generate lists of names or to export the names. Given the data that must be collected for each surgeon and the limited number of surgeons per clinical department, we consider it identifying whether or not it contains the name.

Identifiable data of patients will be stored in a physically separated GCP-compliant database. Access to the database will be restricted to data entry personnel. After the closure of the database containing participant data, each site will receive a list of their patients (participant log) for archiving. After all sites confirmed receipt of their list, the database will be (completely) erased. A codebook describing the set-up of the database will be stored in the Trial Master File. The data on adherence to the StOP?-protocol will be collected via questionnaires filled out by the scrub technicians after each operation (#6). To identify the operation, the scrub technicians will put the patient sticker on the paper questionnaire and deposit the questionnaire in a sealed box within the operation room ward. The paper questionnaires will at no point leave the hospital. The research team will enter the questionnaires into the system, and the data will be coded at this point, so that no identifying information will remain with the electronically stored adherence data.

#### Retention and destruction of study data and biological material

All study data are archived for at least 15 years after study termination or premature termination of the study.

### Further aspects

#### Overall ethical considerations

The expected results may reveal if clinical outcomes can be improved by addressing team behavior during the performance of complex surgical procedures. In particular, the study has the potential to provide evidence that a short (typically between 30 and 90 s) and inexpensive intraoperative briefing may reduce mortality and morbidity. The results of the study will be of interest not only to surgical specialists but also to a wide public, and therefore, progression and findings will be communicated to healthcare workers of other specialties.

#### Risk-benefit assessment

As benefits, we expect that this simple, cost-efficient behavioral intervention will improve the quality of peri-operative communication and consequently reduce the risk of errors associated with the intervention and peri-operative care, eventually reducing post-operative patient mortality, unplanned reoperations, readmissions, and reduce the length of hospital stay. If the study reveals a positive effect not only on mortality, it is likely that the StOP?-protocol has importance for even more types of operations including operations of the head and neck and orthopedic procedures, and it may be extended to disciplines that mainly perform percutaneous interventions such as cardiology, angiology, and neuroradiology that typically are associated with other complications than mortality.

From a clinical perspective, the risks of the study seem minimal. In the StOP? I trial, we did not observe adverse events or risks associated with the intervention itself. The primary treatment is not affected at any time by these interventions. Distraction or irritation of the personnel or prolongation of the surgical procedures because of the briefings has not been observed between the two groups. Surgeons in the intervention group perform the StOP?-protocol according to the manuals and training. We will not define the criteria for modifying the intervention, as the surgeon is allowed to adapt the timing and execution of the protocol according to the procedure. This flexibility of the StOP?-protocol is a central part of the concept. Overall risks of StOP? seem comparable to the risk of conducting preoperative time-out that is now standard worldwide.

However, from a scientific perspective, there are some risks inherent to this study:

*Threat of bias of contamination*: Given that the study aims to change the behavior of surgeons in the treatment group, potential bias or contamination of the surgeons enrolled in the control group needs to be addressed:○ First, surgeons in the control group will not undergo the StOP? training, but they will not be blind to the intervention as surgeons within a department work closely together. This could be a source of contamination, because surgeons in the comparator group may observe StOP?s performed while they operate with a surgeon in the intervention group. If surgeons in the comparator group observe communication behavior that they judge as promising, they may be motivated to copy this behavior. However, sporadic observations of others’ behaviors are not sufficient to sustainably change a behavior. Active strategies are needed to improve adherence to and ensure the sustainability of behavioral interventions, such as audits and feedbacks [46].○ Second, different hospitals will be included in the study and some may already have implemented a sign-out. Surgeons in the intervention group will explicitly be asked to reflect what extent the StOP?-protocol may be associated to the sign-outs, so that both can be combined during the operation in the case they already work with sign-outs. We will record the communication practices of each hospital (including sign-outs) and statistically control for these practices in the analysis.

*Threat of potential interaction between the treatment and the control group*: An important aspect is that surgeons in the comparator group may be operating together with surgeons in the treatment group within a surgical department. Thus, a not trained surgeon may participate in operations where a StOP?-protocol is done; this could lead to direct interactions. As discussed in the section on statistical methods for additional analyses, we expect different interactions (i.e. (i) both surgeons are from the intervention group, (ii) both surgeons are from the control group, and (iii) one surgeon is from the intervention group and the other from the control group). These different interactions were taken into account in the sample size calculation and will also be taken into account in the data analysis and allow for interesting future analyses. 

If a surgeon from the intervention group collaborates with a control group surgeon, we define that during the collaborative phase, the surgeon with a higher hierarchical status acts according to his or her study condition. Thus, an intervention group surgeon with lower hierarchical status will not have to initiate StOP?s in the presence of a control-group surgeon with a higher hierarchical status.

